## Abstract

**Background:**

Patients with stroke should have access to a continuum of care from organized stroke units in the acute phase, to appropriate rehabilitation and secondary prevention measures. Moreover to improve the outcomes for acute stroke patients from an organizational perspective, the use of multidisciplinary teams and the delivery of continuous stroke education both to the professionals and to the public, and the implementation of evidence-based stroke care are recommended. Clinical pathways are complex interventions that can be used for this purpose. However in stroke care the use of clinical pathways remains questionable because little prospective controlled data has demonstrated their effectiveness. The purpose of this study is to determine whether clinical pathways could improve the quality of the care provided to the patients affected by stroke in hospital and through the continuum of the care.

**Methods:**

Two-arm, cluster-randomized trial with hospitals and rehabilitation long-term care facilities as randomization units. 14 units will be randomized either to arm 1 (clinical pathway) or to arm 2 (no intervention, usual care). The sample will include 238 in each group, this gives a power of 80%, at 5% significance level. The primary outcome measure is 30-days mortality. The impact of the clinical pathways along the continuum of care will also be analyzed by comparing the length of hospital stay, the hospital re-admissions rates, the institutionalization rates after hospital discharge, the patients' dependency levels, and complication rates. The quality of the care provided to the patients will be assessed by monitoring the use of diagnostic and therapeutic procedures during hospital stay and rehabilitation, and by the use of key quality indicators at discharge. The implementation of organized care will be also evaluated.

**Conclusion:**

The management of patients affected by stroke involves the expertise of several professionals, which can result in poor coordination or inefficiencies in patient treatment, and clinical pathways can significantly improve the outcomes of these patients. It is proposed that this study will test a new hypothesis and provide evidence of how clinical pathways can work.

**Trial Registration:**

ClinicalTrials.gov ID [NCT00673491]

## Background

Stroke represents one of the major public health problems worldwide. Despite advances in stroke prevention, diagnosis, treatment, and rehabilitation, stroke causes 9% of all the deaths around the world and stroke-related disability has been judged to be one of the most common causes of disability. In industrialized countries stroke remains a major cause of acute hospitalization with mortality rates at 28 days following the acute onset at approximately 20%. This accounts for more than 4% of direct health-care costs [1-3].

The American Stroke Association's Task Force on the Development of Stroke Systems outlined that the obstacles in translating scientific advances into clinical practice for stroke are often related to a fragmentation of stroke-related care caused by inadequate integration of facilities and professionals that should closely collaborate in providing stroke care. This potentially contributes to the high morbidity, mortality and economic cost of this disorder [4]. Other studies also suggest that establishing well-organized and multidisciplinary stroke care can help improve the quality of service delivered and reduce stroke mortality rates [5,6].

According to the Helsingborg Declaration in 2006 on European Stroke Strategies, all patients in Europe with stroke should have access to a continuum of care, from organized stroke units in the acute phase through to appropriate rehabilitation and secondary prevention measures. Consequently to improve the outcome for acute stroke patients, the optimization of the use of multidisciplinary teams, the development of better ways to deliver a continuing stroke education to the professionals and to the public, the implementation of evidence-based stroke care and the evaluation of different models of stroke services were identified as research and development priorities in stroke care from an organizational perspective [7].

A recent review showed that clinical pathways are tools that can help to achieve these goals when applied to stroke care [8]. Clinical pathways are complex interventions for the mutual decision making and organization of care processes for a well-defined group of patients during a well-defined period with the aim of enhancing the quality of care across the continuum by improving risk-adjusted patient outcomes, promoting patient safety, increasing patient satisfaction, and optimizing the use of resources. Their defining characteristics also include an explicit statement of the goals and key elements of care based on evidence, best practice, and patient expectations; the facilitation of communication amongst the team members and with patients and families: the coordination of the care processes by coordinating the roles, and sequencing the activities of the multidisciplinary care team, patients and their relatives; the documentation, monitoring, and evaluation of variances and outcomes; and the identification of the appropriate resources [9].

The purpose of the Clinical Pathways for Effective and Appropriate Care Study was to determine whether clinical pathways could improve the quality of the care provided to patients who have been affected by stroke both in hospital and through the continuum of the care.

### Objectives

The main objective of the trial is to evaluate the effectiveness of the implementation of clinical pathways for acute stroke care and rehabilitation within a sample of Italian hospitals and rehabilitation long-term care facilities. The hypothesis is that clinical pathways would be more effective than usual care in treating stroke patients and that the clinical pathways would reduce both patient mortality and improve patient outcomes.

The secondary objective is to determine whether clinical pathways increase the appropriateness of the care provided to the patients in hospital and through the continuum of the care and its effects on the outcomes.

The third objective is to determine whether clinical pathways help to implement organized care in acute stroke care and rehabilitation facilities and its effects on the outcomes [5].

A pilot study to define baseline levels of performance in acute stroke care and rehabilitation facilities has been described previously in a separate protocol [10].

### Study design

The Clinical Pathways for Effective and Appropriate Care Study was designed as a multi-centre cluster randomized controlled trial, in which the experimental group contains stroke patients treated according to specific clinical pathways, while the control group received usual care. A cluster design was used (with single hospitals and rehabilitation long-term care facilities of the same area as the randomization units) because of the Ethical and logistical issues associated with the implementation of clinical pathways, which involves a series of complex actions at institutional level [11-14].

### Randomization

Thirty four units based in nine Italian Regions were invited to participate in the study (figure 1). Twenty nine units (hospitals and rehabilitation long-term care facilities within the same area) showed interest in the implementation of the clinical pathways for the acute care and rehabilitation of stroke and were assessed for eligibility. The selection of the units was based on the comparability of their location, patient population, facilities and teaching status both for hospitals and rehabilitation long-term care facilities. To participate in the study the administrators of the hospitals and the rehabilitation long-term care facilities had to allow the institution to be allocated to either of the two strategies (clinical pathway or current practice) for a 1-year period and agree not to implement a clinical pathway for the acute care and/or rehabilitation of stroke if assigned to the usual care group.

**Figure 1 F1:**
[figure not shown]
Flow diagram of the progress of the units through the trial.

Nine units were excluded because they did not meet the inclusion criteria and five units withdrew after the project commenced following a decision by their management (three units withdrew after project pre-test and two units withdrew after project kick off). One unit could not provide reassurance that they would not implement a pathway if assigned to the control group and therefore they were not included in the study sample. The remaining units were randomized to either of the two arms. A simple randomization was carried out before the intervention and patient recruitment started, using a computer-generated sequence with allocation concealment. Fourteen units were selected and randomized. Blinding of patients and clinicians was not possible.

### Study evaluations

The primary outcome measure was patient mortality 30-days following the stroke. Thirty-day mortality was defined as the proportion of ischemic stroke events that are fatal within 30 days from the onset. Stroke fatality was chosen as main outcome because it is clinically relevant, objectively measured, and reliably coded [5]. The impact of the clinical pathways, comparing the length of the in-hospital stay, the hospital re-admissions rates, the institutionalization rates after hospital discharge, the patients' dependency levels, and complication rates along all the continuum of the care were also analyzed. The list of outcome indicators is reported in table 1.

**Table 1 T1:** The outcome indicators set

**Indicator**	**Measure**	**Criterion met/expected change**	**Source, Year**
In-hospital death rate within 30 days from admission to hospital	(%)	Differences in rates	Clinical Outcome Working Group, 1995, 1997; NHS Centre for Coding and Classification, 1990
In-hospital death rate within 30 days from stroke attack	(%)	Differences in rates	
Post-discharge death rates (1, 3, 6, 12 months after discharge)	(%)	Differences in rates	
In-patients length of stay	Days	Differences in means	Schmidt WP, 2003
Within 9 days length of stay in hospital patients' rate	(%)	Differences in rates	
Pressure ulcers incidence rate	(%)	0%	Clark M, 1991; Effective Health Care, 1995
Overall in-hospital complications rate	(%)	4%	Adams HP Jr, 2003
Overall post-discharge complications rate	(%)	Differences in rates	
Dependency at discharge	FIM scale	Differences in means	Gompertz P, 1993 Wade DT, 1987
Dependency at 6 months after stroke	FIM scale	Differences in means	Hardwood RH, 1994
Institutionalization at discharge	(%)	Differences in rates	Nikolaus T, 2000 Kalra L, 1995
In-hospital re-admission rate (within 30 days from discharge)	(%)	Differences in rates	Ebrahim S, 1987 Milne R, 1990
Return to pre-stroke functioning in daily life rate (with ADL/case mix adjustment)	(%)	Differences in rates	Early Supported Discharge Trialists (Cochrane 2005, Issue 2)

The quality of the care provided to the patients was assessed by monitoring the use of diagnostic and therapeutic procedures during hospital stay and rehabilitation, and by the use of key quality indicators at discharge as reported in previous studies (table 2). The implementation of organized care was also evaluated (table 3).

**Table 2 T2:** The process indicators set

**Indicator**	**Measure**	**Criterion met/expected change**	**Source, Year**
Information, advice and support from the multidisciplinary team given to the patients (and with their consent, to the carers)	(%)	Given to all the patients/relatives/care givers	SIGN 64, 2002
Use of referral protocols (to neurovascular clinics and admission to stroke unit)	(%)	Given to all the patients	NHS QIS (CSBS-PPI 2002) Clinical Standards, 2004; CHD/Stroke Task Force, 2001; SPREAD, 2005
Use of clinical protocols (at least 5 of the following)	(%)	Given to all the patients	CHD/Stroke Task Force, 2001; CSBS 2002; Antiplatelet Trialists' Collaboration, 1994; SIGN 13, 1997; European Atrial Fibrillation Trial, 1993; Hebert PR, 1997; SIGN 14, 1997; Antithrombotic Trialists' Collaboration, 1998
- Stroke treatment/management protocols			
- Antiplatelet/anticoagulant protocol			
- Diabetes treatment protocol			
- Atrial fibrillation therapy protocol			
- Blood pressure lowering protocol			
- Cholesterol lowering protocol			
- Suspected carotid stenosis protocol			
- Smoking cessation protocol			
Use of (local) admission to social services protocols	(%)	Given to all patients	Report to the Dept. of Health, 2000
Use of CT/MRI brain scan within 48 hours from admission	(%)	80%	SIGN 14, 1997; Wardlaw JM, 2003
Aspirin treatment within 48 hours from admission	(%)	Given to all patients	Gubitz G (Cochrane 2003)
Swallow screen test on day of admission	(%)	Given to all patients	SIGN 20, 1997
Blood pressure assessment	(%)	Given to all patients	Progress, 2001; NHS QIS (CSBS 2002); Clinical Standards, 2004
ECG/ECD within 24 hours from admission	(%)	Given to all patients	SIGN 13, 1997
Continuous monitoring within 48 hours from admission (see parameters below)	(%)	Differences in rates	SIGN 13, 1997; New Zealand Guidelines Group, 2003; Canadian Stroke Network and the Heart and Stroke Foundation of Canada, 2006
- Blood pressure			
- Glycaemia			
- Electrolitemia			
- Breath			
Before discharge total assessment (see parameters below)	(%)	Given to all patients	MRC/BHF Heart Protection Study, 2002, 2003; SIGN 24, 1998
- Tobacco smoke			
- Lipemia			
- Glycaemia			
Use of discharge plan (and communication)	(%)	Given to all the patients/relatives/care givers	SIGN 24, 1998
Use of SIGN guidelines-based discharge plan	(%)		SIGN 24, 1998
Use of discharge summary and information (information pack)	(%)		RCPE, Consensus Panel, Nov 2000; SIGN 65, 2003

**Table 3 T3:** The organized care indicators set

**Indicator**	**Measure**	**Criterion met/expected change**	**Source, Year**
Use of organized care	OCI	Differences in rates	Saposnik G, 2007
Admission to stroke unit	(%)	100%	NHS QIS (CSBS 2002) Clinical Standards, 2004; CHD/Stroke Task Force Report, 2001; SIGN 13, 1997; SIGN 64, 2002
Stay in stroke unit within 24 hours after admission and until the end of in-hospital rehabilitation	(%)	70%	
Use of case managers (physiotherapists, occupational therapists, nurses specialized in stroke care)	(%)	Given to all the patients	RCP IWP/S, 2000; SIGN 64, 2002
Use of stroke team	(%)	Given to all the patients	CHD/Stroke Task Force, 2001; SIGN 64, 2002
Assessment for rehabilitation needs by a member of the stroke team within 48 hours after admission	(%)	Given to all the patients	Brown M, 2000
Patients' needs assessment and planning rate for post-discharge services	(%)	Given to all the patients	RCPE, Consensus Panel, Nov 2000; NHS QIS Clinical Standards, 2004
Follow-up rate within 3 months after discharge (by specialist/stroke team)	(%)	Given to all the patients	

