### Study sample

A calculation was made to identify the sample size needed to detect a statistical difference in the 30-days mortality rate. As between 8% to 17% of ischemic stroke patients die within 30 days of the incident, it was expected that the clinical pathways would succeed in limiting mortality to 8% and would therefore be clinically relevant [3,15,16]. Based on this goal a sample size of 476 patients (238 in each group) was required for the study to have 80% power at the 5% significance level. The sample size calculation was performed according to standard criteria for cluster randomized trials. The sample size was adjusted using an inflation factor of 1.43 to account for the cluster randomization: 7 clusters per trial arm, cluster size of 24 patients, ICC of 0.018 [17-19].

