### Data analysis

Data was prospectively collected by local staff for both the interventions and the control groups (physicians and nurses had been trained prior to commencement of the study at two educational events in order to do this). Incentives for the local staff were not used. Data was collected using a standardized data extraction instrument which utilized web technology. This allowed only data without unique personal identifiers, but with a unique study identification code (and therefore anonymous), to be entered into a secure database housed at the University of Eastern Piedmont.

The analysis will be performed by the research team. In addition to common descriptive statistics (Fisher exact and Kruskal Wallis test for categorical and continuous variables, respectively), that will be performed at the cluster level, the differences in the rate of 30-days mortality across groups and according to each variable under study will be evaluated using random-effects logistic regression, thus accounting for the clustering effect [5,22,23]. Variables will be included if significant at the 0.10 level (backward approach), with the exception of age which will be forced to entry. The presence of multicollinearity, interaction and higher power terms will be assessed to check final model validity.

Statistical significance will be defined as a two-sided p-value < 0.05. All analyses will be intention-to-treat and will be carried out using Statistica statistical software.

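### Mortality beyond 30 days is listed only as deaths after discharge, so the four later rates compare groups the pathway may itself have selected and cannot show whether an early survival gain lasts

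*Protocol article*

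**What the plan says.** Protocol article, Study evaluations, Table 1 has three mortality rows: "In-hospital death rate within 30 days from admission to hospital", "In-hospital death rate within 30 days from stroke attack" and "Post-discharge death rates (1, 3, 6, 12 months after discharge"). For each, the expected change is a difference in rates. The first two are limited to hospital deaths and stop at 30 days. The third fixes its event (death after discharge) and its clock (from discharge) but states no denominator. No row gives cumulative mortality at 3, 6 or 12 months.

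The primary outcome is defined separately in the same section: "Thirty-day mortality was defined as the proportion of ischemic stroke events that are fatal within 30 days from the onset". It counts a death wherever it happens.

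The time of discharge is itself under study. The section describes "comparing the length of the in-hospital stay, the hospital re-admissions rates, the institutionalization rates after hospital discharge", and Table 1 also lists the share of patients with a stay of no more than 9 days.

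Under Objectives the hypothesis is that "the clinical pathways would reduce both patient mortality and improve patient outcomes". Under Study sample, 30-day mortality is put between 8% and 17%, and "it was expected that the clinical pathways would succeed in limiting mortality to 8" per cent. Data analysis names a random-effects logistic model for 30-day mortality and adds: "All analyses will be intention-to-treat".

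**The concern.** Randomization makes the arms comparable at inclusion, not at discharge. If the pathway prevents deaths in hospital, the pathway arm's discharged patients include some who would have died under usual care. The control arm's discharged patients include no counterpart. A post-discharge comparison then mixes the effect of the pathway with a difference in who is at risk. Using all patients as denominator does not cure this, because a patient who died in hospital is then recorded as not having died at 12 months.

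The clock adds to this. A patient who dies on day 20 is an in-hospital death if still an inpatient, and a post-discharge death if sent home on day 9. A shorter stay in one arm therefore moves deaths between rows without changing any date of death.

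At stake is the natural follow-up question to the primary outcome: does an early gain in survival last to 6 or 12 months? Table 1 as written cannot answer it.

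**Working it through.** **Where a death is counted**

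| Death | Primary (30 days from onset) | In-hospital rows | Post-discharge row |
|---|---|---|---|
| In hospital, day 5 | yes | yes | no |
| After discharge, day 20 | yes | no | yes |
| In hospital, more than 30 days after admission and onset | no | no | no |
| After discharge, day 90 | no | no | yes |

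Adding the in-hospital and post-discharge rows leaves a gap (third line). Adding the primary outcome and the post-discharge row counts some deaths twice (second line). No sum of rows gives total mortality.

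**Inputs, per 100 patients per arm.** The plan gives no mortality after discharge, so there is no figure of its own to reproduce.
- 30-day deaths: control 17, pathway 8 (Study sample; 17 is the upper end of the stated range, read as the control rate). Averted: 17 − 8 = 9.
- Assumed: 12-month post-discharge mortality b = 15% in patients who survive under either arm, and m = 30% to 50% in the 9 saved patients.
- Assumed: the pathway does not otherwise change mortality after day 30.

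**Case 1: all 30-day deaths occur before discharge**
- Control: 83 discharged alive; 83 × 0.15 = 12.45 later deaths; 12.45/83 = 15.0%.
- Pathway: 92 discharged alive; 12.45 + 9 × 0.30 = 15.15 to 12.45 + 9 × 0.50 = 16.95 later deaths; 15.15/92 = 16.5% to 16.95/92 = 18.4%.
- All patients as denominator: 12.45% against 15.15% to 16.95%.
- Total mortality: 17 + 12.45 = 29.45% against 8 + 15.15 = 23.15% to 8 + 16.95 = 24.95%. The pathway is truly better by 6.3 to 4.5 points.

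Among patients discharged alive, the pathway rate is (83b + 9m)/92, which exceeds b only when m > b. Over all patients the excess is 9m, positive for any m above zero. With b = 10% and m = 30%: 10.0% against (8.3 + 2.7)/92 = 12.0%, while the totals are 25.3% against 19.0%.

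**Case 2: 60% of 30-day deaths occur before discharge, full 9-point effect kept**
- Before discharge: 10.2 against 4.8. After discharge but by day 30: 6.8 against 3.2. Discharged alive: 89.8 against 95.2.
- The pathway now averts 6.8 − 3.2 = 3.6 deaths that the post-discharge row does count.
- (a) 15% taken as the rate in all control patients discharged alive. Control: 89.8 × 0.15 = 13.47, or 15.0%. Pathway: 13.47 − 3.6 + 2.7 = 12.57, or 12.57/95.2 = 13.2%; up to 13.47 − 3.6 + 4.5 = 14.37, or 15.1%. Totals: 10.2 + 13.47 = 23.67 against 4.8 + 12.57 = 17.37 to 4.8 + 14.37 = 19.17, again 6.3 to 4.5 points better.
- (b) 15% applied only to the 83 alive at day 30 under either arm. Control: (6.8 + 12.45)/89.8 = 21.4%. Pathway: (3.2 + 12.45 + 2.7)/95.2 = 19.3% to (3.2 + 12.45 + 4.5)/95.2 = 21.2%. Over all patients: 19.25% against 18.35% to 20.15%.

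**Case 3: 80% before discharge, basis (b)**
- Before discharge: 13.6 against 6.4. After discharge by day 30: 3.4 against 1.6.
- Control: (3.4 + 12.45)/86.4 = 18.3%. Pathway: (1.6 + 12.45 + 2.7)/93.6 = 17.9% to (1.6 + 12.45 + 4.5)/93.6 = 19.8%. The sign depends on m.

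**A pathway effect after discharge.** In Case 1 the pathway rate falls back to 15% (92 × 0.15 = 13.8 deaths) if later mortality in the other survivors drops to (13.8 − 2.7)/83 = 13.4% at m = 30%, or to (13.8 − 4.5)/83 = 11.2% at m = 50%.

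**The case against.** The case for leaving the row alone has weight. It is labelled post-discharge and measures just that. It sits below two in-hospital rows, and nothing presents it as total long-term mortality. It is one of 13 outcome indicators, is not named in the section's text, and carries no power claim or decision rule. The mortality hypothesis is tested by the 30-day primary outcome. The intervention extends to rehabilitation, so a benefit after discharge is possible and would offset the selection. The document says nothing on later mortality, nor on whether saved patients are frailer.

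Most of this stands, and it rules out four stronger readings that a reader might infer:
- *That an effective pathway will look harmful later.* Cases 2 and 3 show that the sign is not robust. It depends on how many early deaths precede discharge and on assumed later mortality.
- *That deaths are miscounted.* A death in hospital on day 5 is counted in the primary outcome and in the in-hospital rows.
- *That the row contradicts the intention-to-treat statement.* Patients are still analysed in the arm of their unit, and no denominator is stated. The fit is awkward, but there is no contradiction.
- *That the mortality hypothesis goes untested.* The primary outcome is sound on this point.

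The objection does not remove the core. The missing denominator could be left to a fuller document, but either natural choice has a defect, because the row itself fixes the event and the clock.

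**Conclusion.** The point holds for the four secondary post-discharge rates and for nothing else. They are listed for comparison, yet they rest on an event and a start time that the pathway can alter, and Table 1 offers no cumulative alternative.

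The more dependable consequence is that they understate a gain. In Case 2(a) they show between 1.8 points in favour of the pathway and 0.1 against, when the true gain is 6.3 to 4.5 points. Reversal of sign among patients discharged alive, by 1.5 to 3.4 points in Case 1, needs three things together: nearly all averted deaths fall in hospital, saved patients later die more often than other survivors, and other survivors gain nothing after discharge. All later-mortality figures are assumptions. The structural point (selection at discharge, a clock that may shift, and rows that cannot be added) does not depend on them.

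**What to change.** Add a row to Table 1: *cumulative death from any cause by 3, 6 and 12 months from stroke onset, all included patients*. Count deaths in hospital and after discharge together, and analyse it with the clustered random-effects logistic model already planned for 30-day mortality. Make this the between-arm comparison. Keep the post-discharge rates as descriptive figures without between-arm inference.

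The cost is the wording of Table 1 and one derived variable. Onset, discharge and death dates are already needed for the listed indicators, and the table already uses a stroke-based clock for dependency at 6 months. Twelve months from onset falls no later than twelve months from discharge, so follow-up need not be extended; the price is a slightly earlier last time point. The analysis is described as still to be done, so the derivation can be changed.
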